##### Additional quantitative analyses

Treatment credibility, acceptability, and experience scores will be calculated and compared for both treatment groups, using simple mean comparisons. Change in child symptoms and functioning on a sessional basis will be plotted to explore the trajectory of change in the OSI arm.

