### Sample size {14}

Between 418 and 560 children (209–280 per group) with a primary anxiety problem and their parents will be randomised across the two treatment arms. This sample size is considered to be sufficient to provide a standardised noninferiority margin = 0.33 and between 80 and 90% power (allowing for 30% attrition). The required sample size was calculated using PASS 2019.

A sub-sample of up to 20–40 parents and therapists/supervisors from both arms will be involved in qualitative interviews to explore their experiences of treatment. We will purposively sample from parents who have reached 14 weeks post-randomisation until we reach saturation in terms of (i) representation across the sample for geographic, economic, and educational backgrounds and (ii) until no new themes are identified. We will also aim to recruit therapists who reflect differing characteristics (e.g. service provider type and location, demographic factors, and clinical backgrounds), as well as therapists’ supervisors. We have previously found that this number of participants is typically sufficient for data saturation.

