## Assignment of interventions: allocation

### Sequence generation {16a}

Participants will be randomised in a 1:1 ratio to (i) OSI+therapist support or (ii) CAMHS treatment as usual for child anxiety problems within the COVID-19 context (C-TAU).

Minimisation by child age (≤8; ≥9), gender, service type (school based or not school based), and baseline anxiety-associated interference including permuted block size will be used to ensure balance across groups.

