#### Treatment credibility and experience

Credibility and Expectation of Improvement Scale (CEI): Parents will be asked to complete the CEI to assess participant expectations and views regarding treatment credibility, after randomisation and prior to treatment commencing [41]. It consists of three items, rated on a scale from 0 ‘not at all’ to 10 ‘completely’, asking about how logical the treatment seems, confidence in its success at reducing their symptoms, and their likelihood to recommend the therapy to a friend with similar symptoms. This measure is administered after randomisation with reference to the allocated treatment arm.

An adapted version of the CEI will also be administered 14 weeks post-randomisation, to give a retrospective account of treatment credibility (i.e. the questions are reworded to be considered in light of having received treatment).

We have also adapted the CEI to evaluate therapists’ experiences of treatment within this trial. This comprises items referring to how logical they found the treatment, how comfortable they felt delivering the treatment, how prepared they felt, certainty in the success of the intervention, confidence recommending the treatment to other therapists, and likelihood of administering the treatment again. Completion of this is part of their delivery of the research study.

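### Comparing the parent credibility scores by simple means gives up some precision and, at week 14, leaves the arm difference open to bias if non-response is linked to credibility and uneven between arms

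*Protocol article*

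**What the plan says.** Under Additional quantitative analyses the protocol states: "Treatment credibility, acceptability, and experience scores will be calculated and compared for both treatment groups, using simple mean comparisons". It names no covariates, analysis set, test or interval for these scores.

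Parents complete the CEI twice. Of the first occasion, the section Treatment credibility and experience says: "This measure is administered after randomisation with reference to the allocated treatment arm". Of the second: "An adapted version of the CEI will also be administered 14 weeks post-randomisation, to give a retrospective account of treatment credibility". The week-14 questions are reworded to look back on treatment received.

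Allocation is described in Sequence generation {16a}: "Participants will be randomised in a 1:1 ratio", with "Minimisation by child age (≤8; ≥9), gender, service type (school based or not school based), and baseline anxiety-associated interference".

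The clinical outcomes are treated differently. Analysis of clinical outcomes specifies a mixed model adjusted for the stratification variables, with a similar approach for the other secondary outcomes. The CEI is not among the secondary outcomes listed under Outcomes {12}, so that model does not clearly reach it. The missing-data steps in {20c} are written mainly for the primary outcome. The same section allows that response could differ between arms.

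**The concern.** This point is about the parent CEI only. The method is stated, not left open, so a statistical analysis plan that follows the protocol would carry it forward.

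Two kinds of available information go unused. The first is the set of minimisation factors, which are known for every randomised family. The second is the first CEI of a parent who gave it and then did not answer at week 14. A simple week-14 mean can only describe those who answered. If parents who doubted their allocated treatment drop out more in one arm, that arm's mean is pushed up.

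Parents are not blinded and the primary outcome is parent-reported. Readers will therefore look to the credibility comparison when judging whether expectations differed between arms, so it is worth estimating well even as a supporting measure.

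**Working it through.** **Inputs from the protocol.** Sample size {14}: "Between 418 and 560 children (209–280 per group) with a primary anxiety problem and their parents will be randomised", margin 0.33 SD, 80% to 90% power, 30% attrition. The protocol gives no correlation between the two CEI occasions, no variance explained by the minimisation factors and no loss figure specific to week 14. Those are assumptions below. The score SD is set to 1.

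**The plan's own figure.** Per arm, n = 2(z₀.₉₇₅ + z_power)² / 0.33².
- 80% power: 2(1.960 + 0.842)² / 0.1089 gives 145 (146 with the t distribution). Dividing by 0.70 gives 208 (209). Stated: 209.
- 90% power: 2(1.960 + 1.282)² / 0.1089 gives 193 (194). Dividing by 0.70 gives 276 (278). Stated: 280.

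The stated sizes reproduce closely, so 209 and 280 per arm are used below.

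**Step 1: leaving out the minimisation factors.** The arms are balanced on these factors by design, so omitting them does not bias the difference in means. If they explain a share R² of the variance, the unadjusted standard error is too large by 1/√(1 − R²).

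| R² (assumed) | Ratio | Coverage of a nominal 95% interval |
|---|---|---|
| 0.02 | 1.010 | 95.2% |
| 0.05 | 1.026 | 95.6% |
| 0.10 | 1.054 | 96.1% |
| 0.20 | 1.118 | 97.2% |

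The error is always on the conservative side.

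**Step 2: non-response at week 14.** Two correlated scores per parent were simulated with no true arm difference. The chance of answering at week 14 followed a logistic function of the first score. There were 1,500 trials per setting, at 209 and 280 per arm and correlations of 0.3, 0.5 and 0.7. The ranges cover all of these.

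| Non-response | Bias of raw difference (SD) | Coverage of a nominal 95% interval |
|---|---|---|
| 30% in both arms, unrelated to first score | about 0 | about 95% |
| 30% in both arms, same dependence (log-odds 0.7 per SD) | about 0 | about 95% |
| 20% v 40%, same dependence (0.7) | 0.04 to 0.08 | 94% to 86% |
| 30% in both arms, dependence in one arm only (0.7) | 0.05 to 0.14 | 93% to 73% |
| 30% in both arms, dependence in one arm only (1.0) | 0.07 to 0.18 | 91% to 53% |
| 20% v 40%, dependence in the higher-loss arm only (1.0) | 0.10 to 0.23 | 87% to 37% |

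An estimate that regresses the week-14 score on the first score within each arm, and evaluates it at the mean first score of everyone in that arm, stayed within 0.005 SD of zero in every setting.

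A hand check on scale: with 209 per arm and 20% v 40% loss, about 167 and 125 parents respond. The standard error is then √(1/167 + 1/125) ≈ 0.118 SD. A bias of 0.08 SD is about 0.7 standard errors and one of 0.23 SD is about 2, which agrees with the loss of coverage shown.

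**Step 3: why the first CEI must not be a covariate.** It is collected after allocation and rates the allocated arm. With a true difference of 0.30 SD on both occasions and a correlation of 0.5, adjusting for it leaves 0.30 − 0.5 × 0.30 = 0.15 SD. Simulation gave 0.15.

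**The case against.** The case for leaving the plan alone is substantial.

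- **Role of the measure.** The parent CEI is not a listed primary, secondary or exploratory measure, and no decision rests on it. The protocol promises no interval or test for it, so the coverage figures describe only what would follow if an interval were reported. This stands and keeps the point small.
- **Minimisation factors.** A reader might infer that ignoring them biases the comparison. It does not; it costs precision only. Nothing in the documents shows that age, gender, service type or baseline interference predict credibility, so the loss may be near the lower end.
- **Pattern of loss.** A reader might infer that the protocol expects unequal response, or that sceptical parents stop answering. Section {20c} says only that rates could differ, and nothing links response to credibility. The 30% attrition sits in the sample-size section and is not tied to week 14. The one-arm scenarios are unfavourable by construction.
- **First scores.** It is tempting to say that the first CEI of every lost parent is already in hand. Under Participant timeline {13} it is a further questionnaire after randomisation, and it is not a condition of randomisation, so it may be missing too. The near-zero bias of the joint estimate holds because the simulation assumes complete first scores and loss explained by them.
- **Different question at week 14.** The later form looks back on treatment, and treatment may start up to 12 weeks after randomisation. Describing those who answered is a defensible aim.
- **Deferred detail.** The protocol leaves full detail to the analysis plan. That covers analysis sets and reporting, but the comparison method itself is stated here.

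What survives is that the stated method discards usable information and leaves the week-14 comparison without protection against one recognisable form of uneven non-response.

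**Conclusion.** The point holds as a modest improvement to a supporting analysis. Omitting the minimisation factors makes an unadjusted standard error about 1% to 12% too large for R² of 0.02 to 0.20, without bias.

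The week-14 difference is biased only if non-response depends on credibility and differs by arm in rate or pattern. The size is about 0 otherwise, 0.04 to 0.08 SD under a marked imbalance with shared dependence, and up to 0.23 SD in the worst one-arm setting tried. These values rest on assumed correlations of 0.3 to 0.7, assumed loss of 20% to 40% and assumed dependence. The documents supply none of them for the CEI.

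The post-randomisation comparison is unaffected by loss that occurs later. The documents do not support a claim that the planned comparison is necessarily biased, that it inflates a planned test, or that it bears on the non-inferiority conclusion.

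**What to change.** State in the analysis plan that the arm difference in the parent CEI will be reported at each occasion from one model. Both CEI scores are outcomes; arm, time, arm-by-time and the minimisation factors are fixed effects; the covariance between occasions is unstructured, so that the reworded week-14 form has its own mean and variance. Do not enter the first CEI as a covariate. Report the number responding by arm at each occasion, and keep the raw means as description.

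The cost is a sentence or two and one more model, with no new data. There are two limits to state alongside it. Change over time should not be interpreted, because the two forms ask different questions. The gain against non-response applies only to parents who gave the first score, and only so far as that score explains who was lost.

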#### Exploratory measures and objectives

*Exploratory measures:* The following measures are built in to OSI to assess parent-reported child anxiety symptoms (RCADS-P; SCAS-8P), interference (CAIS-P), global (ORS) and goal-based (GBOs) outcomes, and parent experience of the intervention (SRS), during weeks 1–7 of OSI treatment (modules 0–6) to explore the trajectory of change reported within the OSI arm.

*Exploratory objective*: To monitor child outcomes on a session-by-session basis within the novel treatment arm.

*Treatment experience:* We will conduct qualitative interviews with parents and therapists/supervisors between 14 and 26 weeks post-randomisation, and also use a therapist ‘experience of treatment’ questionnaire, measured at the end of treatment.

*Objectives:* To understand therapist and parents’ experiences of treating child anxiety problems in the current context.

*Use of the online intervention:* OSI incorporates routine outcome measures that are used for clinical purposes, but are also available to the research team through the OSI researcher portal in pseudo-anonymised form. Usage data are also available through the OSI researcher portal that provides detailed information on parents’ use of the website: frequency of sessions on the website, time spent on the website, and also time spent on the different activities.

*Objectives:* This information will be used to describe the use of and compliance with the intervention.

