### Participant timeline {13}

Where parents and their children provide online consent or assent, respectively, they will be asked to complete online baseline assessments (all questionnaires), prior to randomisation. After randomisation, parents will be asked to complete a further short questionnaire about treatment expectations and acceptability. Treatment in both arms will be organised by the clinical teams who will be requested to start as soon as possible and at most within 12 weeks of randomisation. Families allocated to the intervention arm will access OSI and a member of the clinical team will provide support as they work through each OSI module. Participating parents and children in both arms (OSI+therapist support and C-TAU) will be sent a link to complete post-treatment and follow-up assessments (questionnaires) online 14 and 26 weeks after randomisation.

Therapists will provide information on COVID-19 treatment as usual for each participant at the start of their treatment within the therapist treatment logs in order for us to be able to describe what services are delivered in the COVID-19 context, specifically the treatment approach being followed, who they are having contact with (e.g. child, parent, both), and for how long.

Therapists will provide brief demographic information at the study outset, will record information on activity with each participating family, and will complete a brief questionnaire about their experience of the treatment after completing treatment with each participating family.

We will also conduct qualitative interviews with a subgroup of parents and therapists/supervisors (*n*= 25–40), between 14 and 26 weeks after randomisation, purposively sampled on the basis of demographics, and we will continue to sample to ensure variability in treatment outcomes across both arms, if possible, to explore and to understand therapist and parents’ experiences of treating child anxiety in this context.

SPIRIT schedule of enrolment, interventions, and assessments

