### Recruitment {15}

Participating families will be identified by their clinical teams. Clinical teams will follow their usual procedures to identify the child’s primary presenting problem. The clinical team will conduct an initial assessment of eligibility according to the inclusion and exclusion criteria. Where the clinical team identifies that the study inclusion criteria are met (and exclusion criteria are not), they will briefly outline the study to the parents. If parents express an interest in the study, they will be asked to provide an email address to which they will be sent a secured link to the study IT system where the parent will be able to access online information sheets which will provide further information about the study and what would be expected of the participants, alongside contact details for the study team (email and phone number) so that they can be contacted to answer any questions. There will also be video information (information sheet text being read aloud verbatim). In addition, there is dedicated, age-appropriate, online information including a video (consisting of the information sheet with text being read aloud verbatim) for the child. The parent will then be invited to provide online consent for themselves and their child. Where parents provide consent, a further email will be sent with a link for the child to provide assent.

Therapists whose role includes delivery of psychological interventions to children with anxiety problems within participating clinical teams will be invited to take part and consenting families will be allocated to these therapists for treatment. Allocation of families to therapists will be managed within participating clinical teams.

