#### Adverse events reporting opportunity

Trial therapists will be asked to report any adverse events that they become aware of while working with families in either arm over the whole treatment period. We will also provide parents and children an opportunity to describe any negative impacts of participating in the study after completing the questionnaires at 14 and 26 weeks and, for participating parents, after completing the qualitative interview. So as not to ‘lead’ answers, we will enquire about both the positive and negative consequences of taking part in the treatment. The research team will regularly review responses to identify any responses that indicate the presence of an adverse event.

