##### Analysis of clinical outcomes

Analysis of the primary outcome will be performed using a generalised linear mixed effects model adjusting for stratification variables, and any baseline variables that are deemed to be highly prognostic of the outcome will be used to determine the treatment effect and 95% confidence interval. The mixed effect models will include the outcome as the response variable, time point, randomised group, and baseline score as fixed effects and a participant-specific random intercept. An interaction between time and randomised group will be fitted as a fixed effect to allow estimation of treatment effect at all time points. Non-inferiority is claimed if the lower limit of the 95% confidence interval around the standardised effect size is −0.33. A *P*-value for non-inferiority will also be calculated. A similar approach will be used for the other secondary outcomes.

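### Therapist experience scores repeat within therapist, yet the between-arm comparison is fixed as simple means with no therapist term (exploratory measure, low priority)

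*Protocol article*

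**What the plan says.** Under Participant timeline {13}, therapists "will complete a brief questionnaire about their experience of the treatment after completing treatment with each participating family". The section Treatment credibility and experience identifies the form: "We have also adapted the CEI to evaluate therapists’ experiences of treatment within this trial". Its items cover how logical the treatment seemed, comfort, preparedness, certainty of success, and willingness to recommend and deliver it again. Exploratory measures and objectives gives its status and timing: the trial will "also use a therapist ‘experience of treatment’ questionnaire, measured at the end of treatment".

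Additional quantitative analyses fixes the method: "Treatment credibility, acceptability, and experience scores will be calculated and compared for both treatment groups, using simple mean comparisons". Since the article's own name for the therapist form uses the word experience, the natural reading is that this sentence covers it.

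On who treats whom, Recruitment {15} says: "Allocation of families to therapists will be managed within participating clinical teams". Implementation {16c} has the allocation emailed to the clinical team. The article does not say whether a therapist treats in one arm or both, how many therapists take part, or how many families each treats.

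**The concern.** The items are largely one person's opinion of a treatment, recorded again after each family. Scores from one therapist are therefore likely to be correlated, and a plain comparison of pooled means gives that no weight. The article handles repeated clinical scores differently: that model has "baseline score as fixed effects and a participant-specific random intercept". Ratings repeated within a therapist get nothing equivalent.

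Therapists are not randomised. Teams assign families to them and are told the arm, although the order of these two steps is not stated. Nothing prevents a therapist from working mainly in one arm, and then personal rating level becomes part of the arm difference.

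At stake is the reading of therapists' experience across arms. The Objectives section wants to understand this in order to inform implementation and continued use of online platforms. The primary outcome is not involved.

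**Working it through.** **The plan's own figure.** The only design calculation is for the primary outcome: margin 0.33 SD, 80% to 90% power, 30% attrition. With one-sided 0.025, n per arm = 2(z₀.₉₇₅ + z_power)²/0.33², which gives 145 at 80% and 193 at 90%. Dividing by 0.70 gives 208 and 276, against 209 and 280 stated. That calculation is sound, and this point does not depend on it. The therapist comparison has no figure of its own.

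**Assumed inputs** (none is in the article): m = 2 to 10 families per therapist, within-therapist correlation ρ = 0.1 to 0.5, total variance 1.

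**Case A: each therapist in one arm only.** Design effect = 1 + (m − 1)ρ. True SE / naive SE = √(design effect). Coverage of a nominal 95% interval = 2Φ(1.96/√(design effect)) − 1.

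| m | ρ | Design effect | True/naive SE | Coverage |
|---|---|---|---|---|
| 2 | 0.1 | 1.1 | 1.05 | 93.8% |
| 4 | 0.3 | 1.9 | 1.38 | 84.5% |
| 4 | 0.5 | 2.5 | 1.58 | 78.5% |
| 10 | 0.5 | 5.5 | 2.35 | 59.7% |

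A simulation with 418 ratings and 4,000 runs gave 84.4% at m = 4, ρ = 0.3.

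On an absolute scale, take 100 therapists with 4 families each, so 200 ratings per arm. The naive SE is √(2/200) = 0.100 SD. At ρ = 0.5 the true SE is 0.100 × √2.5 = 0.158, and a nominal 5% test rejects about 21.5% of the time under no difference.

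**Case B: half the therapists in one arm only, half mixed.** With m = 4 and ρ = 0.5 the variance factor is about (2.5 + 1.0)/2 = 1.75. The SE is about 0.132 and rejection about 14%.

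**Case C: every therapist treats in both arms, with the same arm effect.**
- Families fall to arms at random within therapist: simulated coverage of the naive interval is about 94% to 95% (m = 2 to 6), so it is valid.
- The loss is precision. Information per therapist in a random-intercept model is 0.25(m − 1)/(1 − ρ) + 0.25/(mρ + 1 − ρ). At m = 4, ρ = 0.5 this is 1.5 + 0.1 = 1.6. For 100 therapists the SE is 1/√160 = 0.079 against 0.100, or 21% smaller.
- Arms exactly balanced within therapist: true/naive SE = √(1 − ρ), so the naive interval is 5%, 20% or 41% wider than needed at ρ = 0.1, 0.3 or 0.5.

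**Case D: therapists treat in both arms, but the arm difference varies between them.** With a therapist-by-arm variance of 0.2 (assumed), simulated coverage is 88% to 94% for m = 2 to 6. A random intercept alone would not capture this variation.

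**The case against.** Four points can fairly be made against this.

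- **No interval or test is promised.** The article speaks only of comparing means and states no standard error, test or independence assumption. This stands. A reader might infer that the plan declares the ratings independent or fixes a false-positive rate; it does neither. The point concerns any interval or test that would follow from the stated method.
- **The analysis plan may settle it.** The article calls its statistical section a summary and defers detail to the SAP, which may already handle therapists. That would normally end the matter, but here the article names a method. A therapist-level model would go beyond what it names.
- **Therapists may well treat in both arms.** Families are randomised individually, and therapists report "any adverse events that they become aware of while working with families in either arm over the whole treatment period". This is compatible with crossing without establishing it. If crossing is complete and arm effects do not vary between therapists, the naive interval is about valid and only efficiency is lost. Some items, such as certainty of success, may also vary by case, which would lower the correlation.
- **A random intercept is not a full cure.** This also stands. If therapists work in one arm only, it widens the interval but cannot separate rater from arm. If they work in both, therapist-by-arm variation is needed as well.

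A reader might also carry the criticism over to parent credibility. It does not transfer: one parent rates per family, so there is no repeated rater.

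**Conclusion.** The point holds in a limited form. The article has therapists rate once per family and fixes a between-arm comparison with no therapist term. A method that respects the repetition is better under either arrangement of therapists over arms.

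The size cannot be fixed from the article. Over the assumed ranges, with all therapists in one arm, the standard error would be understated by a factor of 1.05 to 2.35. With therapists in both arms and a common arm effect, the comparison is valid but loses precision. It is tempting to cite the 21.5% rejection rate as the plan's error rate, but that figure needs every therapist to work in one arm, which the article nowhere says.

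The measure is exploratory, no decision rule is attached to it, and the primary non-inferiority conclusion is untouched. Priority is low.

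**What to change.** Under Additional quantitative analyses, and in the SAP, replace the simple mean comparison for the therapist scores with wording such as: therapist experience scores, one record per family, will be compared by a linear mixed model with arm as fixed effect and a therapist random intercept, allowing therapist-by-arm variation where therapists treat in both arms. Therapist-clustered standard errors would be an acceptable alternative. Report the number of therapists and the ratings per therapist by arm. Where therapists work in one arm only, state that rater and arm cannot be separated.

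Optionally, adjust the parent credibility comparison for the factors used at randomisation ("Minimisation by child age (≤8; ≥9), gender, service type (school based or not school based), and baseline anxiety-associated interference"). This is a small gain in precision, not a correction.

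The cost is a sentence or two of analysis wording. Data recording and record keeping gives every therapist a unique ID and has therapist records carry the family's study identifier, so no new data are needed.
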